#### Qualitative Interview

Qualitative exit interviews were conducted with 15 participants in the intervention arm between the posttreatment and follow-up assessments to explore acceptability. Interviews covered overall experiences with the SMART-3RP intervention, as well as feedback regarding the content and format of each individual intervention session (see Multimedia Appendix 2 for the interview guide).

### Data Analysis

The sample size (N=60) was chosen based on studies of similar scope (eg, other pilot behavioral trials funded via the same mechanism) and established guidelines for pilot behavioral studies to establish feasibility [62-64].

To evaluate feasibility as a coprimary outcome, we will assess the number of nurse participants screened, eligible, and enrolled (ie, whether >70% of those screened enroll/agree to participate); the number of treatment sessions (ie, whether >70% of participants randomized to the intervention complete at least 2 out of 3 sessions) and assessment visits completed (ie, whether >70% of all participants complete at least 2 out of 3 assessments) in the intervention arm; assessment duration; and reasons for declining enrollment and prematurely leaving the trial. Acceptability (second primary outcome) will be evaluated using the Client Satisfaction Questionnaire (CSQ-8) [61] and qualitative exit interview data among intervention arm participants. Scores on the CSQ-8 will be categorized into 4 levels of satisfaction: ‘‘poor’’ (score 8‐13), ‘‘fair’’ (score 14‐19), ‘‘good’’ (score 20‐25), and ‘‘excellent’’ (score 26‐32). All qualitative exit interview data will be explored for categories and themes around intervention acceptability. Qualitative data will be analyzed using content analysis, facilitated by the Dedoose software [65], to organize data and facilitate analyses. Two study team members will independently review the transcripts to generate an overarching thematic framework for data interpretation, in which major and minor themes are identified. Thematic frameworks will then be compared for consistency, and discrepancies will be discussed until agreement is reached. Data will be reexamined, messages will be extracted and highlighted, and ongoing discussion between coders will allow for further theorizing and making interconnections between research questions, coding categories, and raw data [66].

With respect to exploratory evaluations of quantitative data and secondary outcomes, we expect to compare each outcome between groups using mixed model regression analyses, with participant ID as a random effect. Fixed covariates will include assessment time point (baseline, posttreatment assessment, and 3-month follow-up) and years working in HIV care. Other covariates, such as education, age, and baseline levels of stress, anxiety, and depressive symptoms, and clinic characteristics (eg, clinic size, availability of equipment, and urban vs peri-urban) will also be considered. We will consider exploratory mediational and moderational analyses, based on procedures outlined by Hayes [67]. We will examine patterns in missing data to see if missingness is related to measured participant characteristics. We will adjust for missing data using multiple imputation, as appropriate. We will also adjust for multiple comparisons using the method of Hothorn et al [68].

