**Methods:**

In phase 1 (Human Research Ethics Committee [Medical] of the University of the Witwatersrand [220813, Johannesburg, South Africa] and the Massachusetts General Brigham Institutional Review Board [2022P002765, Boston, Massachusetts, United States]), we conducted 3 focus group discussions to solicit feedback on the lived experiences of stress, sources of stress, impact on job functioning, coping strategies, the proposed intervention, and recruitment strategies for nurses. These data informed adaptations to the intervention. In phase 2 (Human Research Ethics Committee [240106, Johannesburg, South Africa]; Massachusetts General Brigham Institutional Review Board [2024P001407, Boston, Massachusetts, United States]), we conducted a small proof-of-concept study (N=8) with preintervention and postintervention assessments, 6 intervention sessions with a nurse interventionist, and a qualitative exit interview. Following appropriate adaptations, we conducted a pilot randomized controlled trial (N=60) in which participants were randomized to the intervention or the control condition. The control condition received a one-time, 90-minute didactic stress management session. The intervention condition consisted of two 4-hour group skills-based sessions on the relaxation response, components of stress, recuperative sleep, mindful awareness, resilience, and social support. Sessions included practice-based exercises and videos to complement the intervention materials. Baseline, posttreatment (intervention only), and follow-up assessments, as well as qualitative exit interviews (n=15, intervention only), were conducted. Primary outcomes are feasibility (number screened, eligible, and enrolled; the number of treatment sessions and assessments completed in the intervention arm; assessment duration; and reasons for declining enrollment and prematurely leaving the trial) and acceptability (Client Satisfaction Questionnaire-8 and qualitative data).

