A semistructured FGD guide (Multimedia Appendix 1) was developed by the study team based on a review of the existing literature and potential logistical issues that could impact intervention delivery. FGDs gathered information across three domains relevant to SMART-3RP intervention adaptation and implementation: (1) role of culture, perceptions, and experiences of stress; sources of stress (eg, occupational, trauma-related, structural); how stress impacts job functioning (specifically patient care); and current coping strategies; (2) recommendations about the intervention (eg, modules and content, number of sessions, session duration, program length, mode of delivery [virtual, in-person, hybrid approaches], and use of coaches); and (3) the most effective means to recruit professional nurses for a future clinical trial, including minimizing the possibility of coercion and ensuring nurses do not feel “blamed” for insufficient resilience. Most participants preferred an in-person, group format, believing this would enhance their interaction with one another as well as allow for open dialogue and deeper engagement with SMART-3RP material. Participants stressed the importance of (1) having an interventionist present to answer questions and facilitate engagement, (2) ensuring support from clinic management, which would communicate the value of the program to both staff and patients, and (3) normalizing discussions about stress. Participants were supportive of using texting platforms (eg, WhatsApp) to maintain connectedness with other participants and support ongoing skill use.

Changes to the content of the intervention were made based on the FGD results [49]. These included (1) integrating the normalization of stress and talking about stress, (2) discussing the importance of stigma awareness in patient care, (3) integrating an overview of practicing empathy and compassion in patient care while under high pressure, and (4) integrating examples with local imagery for relaxation exercises and adapting food and physical activity guidelines to match the guidelines for South Africa. Additionally, the intervention format was changed from 3 to 6, 1-hour each, in-person group sessions to accommodate the availability of staff to attend the sessions in the midst of a heavy workload and to avoid disrupting patient flow.

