#### Refinement of the SMART-3RP Intervention

Additional changes were made to the intervention format and the protocol based on data from the proof-of-concept study and concurrent changes in health care delivery conditions in South Africa. Specifically, following the proof-of-concept study, South Africa experienced a large wave of layoffs among nurses providing care to people living with HIV due to reduced availability of funding that supports health care infrastructure in South Africa (eg, cuts to President’s Emergency Plan for AIDS Relief and US Agency for International Development); there was also concern that the grant would be terminated. To increase participant outreach and collect as much data as possible before a potential grant termination, the study team changed the format of the intervention to two 4-hour sessions and allowed for the participation of nurses who had recently been laid off but otherwise met the inclusion criteria.

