##### Intervention Condition

The intervention condition consisted of two 4-hour interventionist-led group sessions. The sessions provided information on topics including the RR, the components of stress, recuperative sleep, mindful awareness, resilience, and social support (see Table 1). Sessions also included practice-based exercises (eg, breathing exercises and mindfulness exercises). Short videos were recorded and included in the sessions to complement the material on breathing, thought records (ie, a practical way to capture and examine thoughts), energy battery (ie, awareness of things that add to or deplete their personal battery), social support, mindfulness, and RR exercises. Participants were provided with a manual describing session content and audio recordings of RR exercises. Participants were encouraged to complete practice notes between and after sessions, which corresponded with intervention modules (eg, relaxation practice) to document their goals and progress.

**Table 1. T1:** Adapted Stress Management and Resiliency Training-Relaxation Response Resiliency Program chapters and goals for the intervention arm.

Chapter title	Goals
Stress management and resiliency training	Introduce the SMART-3RP^a^ Introduce the Science of Mind-Body Medicine and its components: Stress Response, the Fight-or-Flight Response, and the RR^b^ Introduce Stress Management and Resiliency Training goals strategy Introduce RR-elicitation method: single pointed focus meditation, body and breath awareness, letter to yourself exercise Establish program and weekly goals
The RR	Introduce RR-elicitation method: autogenic training Introduce “MINIs”^c^ as a method to reduce tension and anxiety throughout the day Introduce the concept of appreciation Discuss recuperative sleep and sleep tips Introduce the Stress Warning Signals exercise
Stress awareness	Introduce mindfulness Introduce RR-elicitation method: mindful awareness MINI^c^ Learn the types of social support Identify what you need and what is feasible Discuss empathy and compassion
Mending mind and body	Introduce new RR-elicitation method: chair yoga Use strategies for applying mindful awareness in daily living Introduce the Pause, Breathe, Reflect, and Choose routine Reflecting on what’s important exercise

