Creating adaptive perspective	Introduce new RR-elicitation method: loving kindness meditation Use cognitive reappraisal as a way to build adaptation Discuss negative automatic thoughts and thinking errors Learn about different coping styles: problem-solving and acceptance-based coping Explore the development of acceptance, an essential quality of acceptance-based coping
Promoting positivity	Introduce RR-elicitation method: idealized self Identify how positivity can increase resiliency in the long term Learn concepts and strategies for enhancing positivity Review SMART-3RP strategies learned Develop a plan for continuing to use program strategies Set goals for the future

a SMART-3RP: Stress Management and Resiliency Training-Relaxation Response Resiliency Program.

b RR: relaxation response.

c MINI: Mindfulness, Intention-setting, Nurture a hobby, Indulge in gratitude.

Participants also had the option of accessing a closed (eg, limited to group members from their cohort) WhatsApp group moderated by the interventionist. The interventionist initiated chats in between group sessions to provide support to participants in practicing stress management skills (eg, “What skills have you been able to practice?” and “Is there a skill that you need some support in using?”). In addition, the interventionist shared the recordings of the RR exercises and the short videos in the WhatsApp group on a weekly basis as a reminder to practice the RR exercises and maintain engagement with the participants.

All intervention sessions were delivered by a professional nurse who was trained on the intervention material and closely supervised by a clinical psychologist. Training sessions took place during the weeks leading up to and during the intervention delivery to review and practice the intervention content and to discuss strategies for delivering the intervention and facilitating group member comfort, participation, and cohesion. The interventionist offered 2 booster sessions, at approximately 1 month from the conclusion of session 2, to reinforce the intervention content and resiliency strategies. Participants were asked to sign a confidentiality statement prior to the inception of group sessions.

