## Results

Eight participants were recruited for the proof-of-concept trial, of whom 100% were female, 75% (n=6) identified as Black, and 75% (n=6) had at least 6 years of experience providing HIV care. All screened participants enrolled, and 100% (N=8) of participants completed at least half of the intervention sessions and at least 2 out of 3 assessments. With respect to acceptability, satisfaction with the intervention was rated as “excellent” on the CSQ-8 (mean 29.25, SD 1.98). Exit interview data highlighted the need for flexibility in intervention delivery (eg, offering multiple opportunities to attend sessions and online content) to support feasibility. Exit interview data also indicated that group sessions were the only space dedicated to the nurses’ well-being, that awareness of the stress experiences of their colleagues led to increased compassion for colleagues, and that relaxation strategies helped support positive engagement with patients during challenging clinical encounters.

Sixty participants have been enrolled in the RCT. As described above, due to concerns around funding and possible study termination, all participants have completed intervention delivery and follow-up assessments. We are currently in the process of data analysis and offering control participants the intervention content. We expect data analysis to be completed in approximately August 2026, at which time we expect to present data consistent with the analyses presented in the *Data Analysis* section.

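### The coprimary session-completion criterion counts two of three sessions, but the RCT intervention had two core sessions plus two boosters, so the rule must be restated on what was delivered

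*Protocol article*

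**What the plan says.** Under Data Analysis, the protocol article introduces its feasibility measures with "To evaluate feasibility as a coprimary outcome". The session component is "whether >70% of participants randomized to the intervention complete at least 2 out of 3 sessions".

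Three places describe the RCT intervention, and they agree with each other:

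- Abstract, Methods: "The intervention condition consisted of two 4-hour group skills-based sessions".
- Refinement of the SMART-3RP Intervention: "the study team changed the format of the intervention to two 4-hour sessions".
- Intervention Condition: "The intervention condition consisted of two 4-hour interventionist-led group sessions".

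The Intervention Condition section then adds: "The interventionist offered 2 booster sessions, at approximately 1 month from the conclusion of session 2". It does not say whether boosters count towards completion.

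A three-session format is mentioned only as history, under Focus Group Discussions: "the intervention format was changed from 3 to 6, 1-hour each, in-person group sessions". The Refinement section replaced that format in turn.

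For the proof-of-concept study, the Results section reports a different session rule: all eight participants "completed at least half of the intervention sessions and at least 2 out of 3 assessments".

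**The concern.** The criterion has a numeric bar and sits inside a coprimary outcome, but its denominator matches no session count given for the RCT. Someone applying it has to choose a substitute, and the candidates differ in how demanding they are. Requiring both core sessions means full attendance. Requiring one of two means half the core content. Counting any two of four lets a nurse who attended one core session and one booster qualify.

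Timing matters too. The Results section says intervention delivery and follow-up are complete and analysis is under way. A rule interpreted now may be interpreted with attendance already known. Since the pilot exists to judge feasibility before a larger trial, a session criterion that readers cannot trace to a fixed definition weakens the main conclusion.

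**Working it through.** **Step 1: try to reproduce the denominator of 3.** Core sessions (Intervention Condition): 2. Core plus boosters (same section): 2 + 2 = 4. Neither is 3.

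**Step 2: list the readings.**

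- Both of the two core sessions: the literal minimum of two, applied to the core programme.
- At least one of two: the proof-of-concept rule of at least half, carried over.
- At least two of four, with boosters counted.
- Two of three, as printed, kept only for comparison.

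**Step 3: an example without a model.** The article gives 60 nurses in total and no arm sizes, so assume 30 in the intervention arm. Exceeding 70% needs at least 22 completers (21/30 is exactly 70%; 22/30 = 73.3%). Suppose 20 attend both core sessions, 8 attend one and 2 attend none.

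- Both of two: 20/30 = 66.7%, fail.
- At least one of two: (20 + 8)/30 = 93.3%, pass.
- Two of four: the 20 already qualify. If only two of the eight single-session nurses attend a booster, the count is 22/30 = 73.3%, pass.

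**Step 4: how far the readings diverge.** Let *p* be the attendance probability per session, assumed independent between sessions. The article gives no *p*; the range examined is 0.60 to 0.95. The probability *q* that one nurse is a completer is:

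- both of two: p²
- one of two: 1 − (1 − p)²
- two of three: p³ + 3p²(1 − p)
- two of four: 1 − (1 − p)⁴ − 4p(1 − p)³

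The chance of meeting the criterion is the binomial probability of at least 22 completers out of 30.

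| Reading | q at p = 0.80 | P(pass), p = 0.70 | P(pass), p = 0.80 | P(pass), p = 0.95 | p at which q = 70% |
|---|---|---|---|---|---|
| Both of two | 0.640 | 0.006 | 0.19 | 0.998 | 83.7% |
| One of two | 0.960 | 0.999 | about 1.00 | about 1.00 | 45.2% |
| Two of three (as printed) | 0.896 | 0.82 | 0.997 | about 1.00 | 63.7% |
| Two of four | 0.973 | 0.999 | about 1.00 | about 1.00 | 50.8% |

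**Step 5: sensitivity to arm size.** At p = 0.80, with 20 nurses (15 needed) or 40 nurses (29 needed), the both-of-two reading passes with probability 0.22 or 0.17. The other three pass with probability at least 0.986.

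**The case against.** The strongest reply is that the rule can still be used: a minimum of two, set against two core sessions, means both. That stands. A reader might infer that the criterion cannot be applied at all, and the document does not support that. However, this reading turns a two-thirds rule into full attendance and raises the break-even attendance from 63.7% to 83.7% per session. The article does not say this was intended.

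A second reply is that the two boosters, placed at a single time point, might be alternative dates for one session, giving 2 + 1 = 3. The text does not say so; it says two booster sessions were offered.

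A third concerns the modelled figures. Attendance of 80% is an assumption, and so is independence. Within-person correlation ρ would give P(both) = 0.64 + 0.16ρ at p = 0.80, which reaches 0.70 at ρ = 0.375. This stands: the figures illustrate divergence and predict nothing. The example in Step 3 needs neither assumption, only an arm size.

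A fourth is that session completion is one of several feasibility measures, with no hypothesis test attached. This is true and limits the reach of the error, but the component has its own stated bar and that bar does not match the trial.

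A reader might also infer that the 3 is left over from the superseded format, or that a favourable definition has been chosen after seeing the data. The first is plausible but unstated. Nothing in the article shows the second.

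**Conclusion.** The point holds as an inconsistency in a coprimary threshold: the denominator of 3 fits neither the two core sessions nor the four sessions including boosters. It rests on the article's own counts and needs no assumption.

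The effect on the result is conditional. With attendance of roughly 60% to 85% per session, the readings can reverse the verdict, as 66.7% against 93.3% shows for an assumed arm of 30. At about 95% attendance the choice hardly matters. The divergence is similar for 20 to 40 nurses in the arm. The article does not report RCT attendance, so whether the choice matters in practice is unknown. The criterion should be corrected before the feasibility result is reported.

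**What to change.** Restate the criterion on the sessions delivered: more than 70% of all nurses allocated to the intervention attend both core sessions, with boosters reported separately and not counted. This keeps the literal minimum of two, and the text should acknowledge that it is stricter than two-thirds. If the sponsor had fixed another rule before seeing attendance, such as at least half, state that rule and its date instead.

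Whatever the rule:

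- Report how many allocated nurses attended 0, 1 or 2 core sessions, and booster attendance, with exact 95% confidence intervals for the proportions, so that readers can apply any of the readings.
- Disclose that the criterion was restated after the format change, and whether attendance data had been seen by then.

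The cost is a sentence or two in the analysis plan and one small table. No new data should be needed, since delivery is complete and the plan already commits to assessing sessions completed. The drawback is the stricter bar, which the full distribution puts in context.

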### Data Management

Quantitative data were collected by trained study staff and entered into REDCap (Research Electronic Data Capture) data management system using encrypted tablets and computers. All tablets were encrypted to the highest standard. Qualitative data were collected by trained study staff, and deidentified transcripts will be coded using Dedoose software [65] to facilitate analyses. Data files were sent to the investigators from the site via secure file transfer.

### Ethical Considerations

All research was performed in accordance with the Declaration of Helsinki and approved by local and international ethics committees. Ethics approval for the study protocol was obtained from the Human Research Ethics Committee (Medical) of the University of the Witwatersrand (240106, Johannesburg, South Africa Provincial Department of Health, the Massachusetts General Brigham Institutional Review Board (2024P001407, Boston, Massachusetts, United States), and letters of support obtained from the District and supporting organizations. Study updates and final findings will be communicated to study participants. All data shared between study sites are fully deidentified. Consent procedures complied with Institutional Review Board requirements by ensuring that participants had the option to opt out without adverse consequences (ie, affecting their employment). Study updates and deidentified findings will also be shared at Data and Safety Monitoring Board (DSMB) meetings organized by the Principal Investigator and the Community Advisory Board meetings convened quarterly at Wits Match Research Unit. Lastly, data will also be presented at national and international scientific meetings and conferences and published in peer-reviewed journals.

We have convened a DSMB comprised of individuals from South Africa with relevant expertise to this study; meetings are conducted in accordance with a DSMB manual outlining the responsibilities of the DSMB, DSMB meeting procedures, and templates for DSMB reports (developed in collaboration with the DSMB members). The investigators are responsible for compiling and submitting annual reports. The DSMB members have reported no conflicts of interest, and their membership was approved by the funder. The DSMB has met twice to allow for additional, external review of study procedures and participant safety. No significant safety concerns were identified. The charter for this study can be requested from the corresponding author.

